### 3.1. Echocardiographic Analysis

A detailed and thorough transthoracic echocardiographic evaluation will be conducted within 48 h of admission after undergoing coronary angiography. All transthoracic echocardiographic studies will be performed by certified operators using high quality equipment (Vivid E95 and Vivid S70, GE Healthcare, Chicago, IL, USA). Offline analysis with proprietary software will be performed using electrocardiogram-triggered echocardiographic data in a cine-loop format and analyzed by EchoPac software version 206 (GE Vingmed Ultrasound). In particular, strain analysis will be performed by Automated Functional Imaging software (GE Healthcare) via the EchoPac software version 206 (GE Vingmed Ultrasound). All the analyses will be conducted by two dedicated cardiologists with expertise in imaging, blinded to the participants’ clinical information. 

Cardiac chamber linear dimensions, volumetric quantification and Doppler analysis will be performed in line with current recommendations [15,16]. The LVEF will be calculated using Simpson’s biplane method. Diastolic function indices will be assessed as per contemporary recommended criteria [16]. Among others, indices of mitral inflow, annular tissue velocities, and the derived trans-mitral to averaged mitral annulus lateral and septal early diastolic velocity ratio (E/e’) will be evaluated. Indices of right ventricular (RV) performance, such as fractional area change (FAC), tricuspid annular plane systolic excursion (TAPSE), systolic movement of the RV lateral wall using tissue Doppler imaging (S’), and pulmonary artery systolic pressure (PASP), will be measured [17].

Longitudinal strain of the LV, RV and left atrium (LA) will be measured by two-dimensional speckle tracking echocardiography. To obtain images of the LV, the apical two-, three- and four-chamber views will be used. Images of the LA will be acquired via the apical two-chamber and four-chamber view. The apical four-chamber RV-focused view will be utilized for the RV. To determine the GLS, the peak systolic longitudinal strain of all segments will be averaged and calculated for each chamber. 

Myocardial work indices for the LV will be calculated non-invasively using a vendor-specific commercially available software package. To determine the parameters of myocardial work, peak systolic LV pressure and GLS of the LV will be incorporated into the formula outlined in a previous study [10]. Four distinct parameters of myocardial work will be computed: (a) LV global work index (mmHg %), which represents the overall work encompassed by the LV pressure–strain loops; (b) LV global constructive work (LVGCW, mmHg %), which is the work accomplished in systole during myocardial shortening as well as the lengthening of the myocardium in the period of isovolumic relaxation; (c) LV global wasted work (LVGWW, mmHg %), which reflects the work of inappropriate systolic myocardial lengthening and myocardial shortening in the isovolumic relaxation period; and (d) LV global work efficiency (%), denoting the proportion of appropriately utilized work by the LV myocardium, calculated using the equation: (LVGCW/[LVGCW + LVGWW]) × 100%.

The analysis of indices for myocardial work of the right ventricle will be conducted by modifying a proprietary software initially developed for assessing left ventricular myocardial work, as explained in a previous study [11]. Similar to the non-invasive approach for evaluating left ventricular myocardial work introduced by Russel et al., the software estimates force-segment length loops for the right ventricular myocardium using pressure–strain loops [10]. Instead of systolic and diastolic blood pressure, the software takes into account PASP and pulmonary artery diastolic pressure (PADP). Pulmonary artery mean pressure (PAMP) is derived using the following equation: the average gradient between the right ventricle and the right atrium plus the mean pressure of the right atrium [18]. The mean right ventricular–right atrial pressure is calculated by analyzing the tricuspid regurgitation velocity–time integral. PADP is estimated as PADP = 1.5 × [PAMP − (PASP/3)] [15,18].

The RV GLS, PASP, and PADP measurements are derived using of right heart valve events. This synchronization enables the generation of pressure–strain loops for the RV, which are derived non-invasively. The analysis of these loops allows for the derivation of four distinct parameters that assess RV function in a manner similar to that for the LV parameters mentioned above.

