### 3.2. Statistical Analysis

The baseline clinical, echocardiographic, laboratory and angiographic features will be examined and compared by the chi-square test for categorical variables for each group. Student’s t-test, or the analysis of variance (ANOVA) will be used for continuous variables. When assumptions of normality are not met, non-parametric tests (Mann–Whitney U, Wilcoxon etc.) will be performed. Continuous variables will be represented by mean ± standard deviation (SD) or median (1st–3rd quartile). Categorical variables will be summarized by frequencies and percentages (%).

Univariable and multivariable logistic regression analyses, and Cox regression analyses will be applied to identify independent predictors at follow-up. Multivariate models will include only the co-variates that are significantly associated with the endpoint at univariate analysis. Receiver operating curves will evaluate the specificity and sensitivity of the resulting echocardiographic, clinical, angiographic and laboratory biomarkers for the prediction of early and late mortality, and rehospitalization. A likelihood ratio test will be used to assess the additional increase in the chi-square value in order to evaluate the potential incremental prognostic value of novel imaging or laboratory parameters over baseline models. To assess the clinical prognosis of several groups of patients with specific echocardiographic or laboratory characteristics, a time-to-event analysis will be performed according to the Kaplan–Meier method. A log-rank test will be used to compare the event rates. The significance threshold for all statistical tests will be considered the two-tailed *p* value of 0.05. The outcomes will be reported with 95% confidence intervals. Data management and statistical analyses will be conducted using SPSS software, version 26 (IBM SPSS Statistics) and R version 3.4.4 (R Foundation for Statistical Computing, Vienna, Austria). 

To calculate the sample size of the study, the G*Power software version 3.1.9.6 was used. It was estimated that to detect an odds ratio > 1.5, approximately 500 patients with AMI will be required with a power of 90%, a statistical significance level < 0.05 and assuming a dropout rate of 20%. The sample size calculations were based on previously published studies on the evaluation of myocardial work indices in patients with AMI [19,20].

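### Choosing covariates by univariable significance alone lets structurally dependent LV work indices share one model, which can hide a truly prognostic index

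*Protocol article*

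**What the plan says.** Section 3.1 states that "Four distinct parameters of myocardial work will be computed" for the left ventricle: global work index, constructive work, wasted work and work efficiency. Their common source is explicit: "peak systolic LV pressure and GLS of the LV will be incorporated into the formula outlined in a previous study". The global work index is described as the quantity "which represents the overall work encompassed by the LV pressure–strain loops". Efficiency is "calculated using the equation: (LVGCW/[LVGCW + LVGWW]) × 100"%. For the right ventricle the loops yield "four distinct parameters that assess RV function in a manner similar to that for the LV parameters mentioned above".

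Section 3.2 states the purpose of the regression models: logistic and "Cox regression analyses will be applied to identify independent predictors at follow-up". The entry rule is: "Multivariate models will include only the co-variates that are significantly associated with the endpoint at univariate analysis". Section 3.2 also plans a likelihood ratio test to "evaluate the potential incremental prognostic value of novel imaging or laboratory parameters over baseline models".

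The sample size in Section 3.2 is about 500 patients, to detect an odds ratio above 1.5 with 90% power, a 0.05 significance level and 20% dropout. It is said to rest on earlier studies of myocardial work. Section 4 describes two such studies, one supporting efficiency and the other the global work index.

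**The concern.** A significance screen tends to admit related variables together. If one work index predicts death, the indices correlated with it, and GLS and LVEF, are likely to pass as well. Nothing in the stated rule then separates them. In a joint model, the coefficient for an index is its effect with its own components or close relatives held fixed. That is not the clinical question, and its standard error is inflated.

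Myocardial work is one of the study's main novel predictors: it is named in the stated goal at the end of the Introduction, and the sample size rests on it. At stake is a report that an index is not an independent predictor, when the result reflects what else was in the model rather than a lack of prognostic value.

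**Working it through.** **1. Structural dependence (from Section 3.1).** Efficiency = 100 × constructive / (constructive + wasted). Given constructive and wasted work, efficiency carries no further information. The relation is nonlinear, so a model with all three can still be fitted, but with inflated variances. The article gives no equation for the global work index. Treating it as roughly constructive minus wasted work plus noise is an assumption.

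**2. The plan's own figure.** The event rate and the unit of the odds ratio are not stated, so 500 cannot be reproduced from the article alone. For one continuous predictor, per SD:

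n = (1.960 + 1.282)² / [p(1−p) × (ln 1.5)² × (1−R²)]

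where R² is the predictor's squared multiple correlation with the other covariates. With an assumed p = 0.20 and R² = 0: 10.51 / (0.16 × 0.1644) gives 400, and 400/0.8 = 500. At p = 0.15 the enrolled number would be 628, and at p = 0.10 it would be 889. The match at 20% contains no allowance for correlated covariates.

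**3. Power as R² rises, starting from the planned 90%.** Power = Φ(3.242 × √(1−R²) − 1.960).

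| R² | Power | Enrolment to keep 90% |
|---|---|---|
| 0 | 90% | 500 |
| 0.5 | 63% | 1000 |
| 0.8 | 31% | about 2500 |
| 0.9 | 18% | about 5000 |

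Power reaches 50% at R² = 1 − (1.960/3.242)² = 0.63, which is a correlation of about 0.80 with a single sibling index.

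**4. Simulation of the rule with LV indices, GLS and LVEF.** Assumptions, none from the article:
- 400 evaluable patients, 10–20% mortality, one index driving death at OR 1.5 per SD.
- GLS 14 ± 3.5%; systolic pressure 125 ± 17 mmHg.
- Constructive work = GLS × pressure with 6% error; wasted work lognormal (median 110, log-SD 0.55).
- Global work index = constructive − wasted − 100 + noise of SD 60, 150 or 250.
- Efficiency by the article's formula; LVEF correlated 0.74 with GLS.

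The implied correlations are about 0.9–0.98 for global work index with constructive work, and −0.83 for wasted work with efficiency. Every variable with univariable p < 0.05 entered one model. Two or more work indices passed the screen in 57–92% of runs.

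| True driver | Significant in joint model | Significant with LVEF only |
|---|---|---|
| Global work index | 4–31% | 49–77% |
| Efficiency | 14–21% | 77–93% |
| Wasted work | 39–53% | not computed |

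Repeats of this set-up with 200 to 500 runs per setting moved the edges: 1–31% for the global work index and 9–24% for efficiency in the joint model, and 41–83% and 68–93% with LVEF only. The summary ranges are therefore rounded.

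**5. Simulation with different assumptions.** Four LV indices only, event rate 20%, constructive–wasted correlation set at −0.3, 0 or 0.3, and noise in the efficiency formula. Variance inflation with all four in the model was about 6–94 for global work index and constructive work, and about 5–10 for wasted work and efficiency. Once it had entered, the true driver stayed significant in 4–32% (global work index), 8–36% (constructive work), 23–49% (efficiency) and 49–64% (wasted work). The direction agrees; the efficiency figure depends clearly on the assumed correlation.

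**The case against.** **The rule does not force joint entry.** A reader might infer that every significant index must go into the same model. The text does not say so: univariable significance is a necessary condition for entry, and models are in the plural. This stands. Joint entry is the natural reading, not a certainty.

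**Another route is planned.** The likelihood ratio test over baseline models can assess an index without its siblings, and Section 4 describes the two cited studies as each assessing one index against LVEF and GLS. Kaplan–Meier and ROC analyses do not depend on joint coefficients, and collinearity harms a prediction model much less than it harms coefficients. This stands in part: the test escapes the problem only if indices are added one at a time, and it does not replace the models assigned to name independent predictors.

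**The four indices are not all near-duplicates.** That stronger reading is tempting but unsupported. Constructive and wasted work are defined as different quantities. Under the assumptions of step 4 they correlate at 0.00; global work index with wasted work is −0.14, constructive work with efficiency 0.46, and global work index with efficiency 0.52–0.57. Only two of the six pairs are close.

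**Sign reversal is not evidence of harm.** If one index drives death, its siblings have conditional effects near zero. With two such terms and independent chance signs, 1 − 0.5² = 75% of runs would show at least one wrong sign without any collinearity.

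**The RV claim is by analogy.** It rests on one sentence in Section 3.1 and was not quantified.

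**Not all of the loss comes from sibling indices.** With the index, LVEF and GLS in the model, significance was 21–64% for the global work index and 59–82% for efficiency, so overlap with GLS takes part of the power.

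**This may be detail for an analysis plan.** A lead index and a collinearity threshold often are, and their absence alone would be no finding. Here, though, the article does state an entry rule, and that rule chooses poorly among these variables.

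**Conclusion.** The point holds as a correctable weakness in a stated rule. Applied in its natural reading, Section 3.2 would often deny independent status to a truly prognostic global work index or efficiency, the two indices for which Section 4 cites evidence. Their chance of remaining significant falls from about 45–80% and 70–93% (with LVEF only) to roughly 4–31% and 10–25%. For efficiency the loss was smaller under the second set of assumptions, and wasted work loses less under both.

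These sizes rest on assumed means, SDs, correlations, event rates and a per-SD odds ratio of 1.5. The structural dependence and the entry rule come from the article. The conclusion does not extend to a claim that the study cannot detect the value of myocardial work.

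**What to change.** Amend Section 3.2 to state:
- At most one LV and one RV work index enters any multivariable model.
- The LV index is named in advance: efficiency or the global work index.
- The other indices are fitted in separate models over the same fixed covariates.
- Whether myocardial work as a whole adds information is tested by one joint likelihood ratio test of the index block over the baseline model, not by individual coefficients.

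This changes analysis wording only, with no new data or patients. Naming the index in advance also prevents choosing it after results are seen. The downside is less power if another index is the true driver. The block test covers that case in part: under the assumptions of step 4, a four-degree-of-freedom test over LVEF rejected in 25–75% of runs.

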### 3.2. Statistical Analysis

The baseline clinical, echocardiographic, laboratory and angiographic features will be examined and compared by the chi-square test for categorical variables for each group. Student’s t-test, or the analysis of variance (ANOVA) will be used for continuous variables. When assumptions of normality are not met, non-parametric tests (Mann–Whitney U, Wilcoxon etc.) will be performed. Continuous variables will be represented by mean ± standard deviation (SD) or median (1st–3rd quartile). Categorical variables will be summarized by frequencies and percentages (%).

Univariable and multivariable logistic regression analyses, and Cox regression analyses will be applied to identify independent predictors at follow-up. Multivariate models will include only the co-variates that are significantly associated with the endpoint at univariate analysis. Receiver operating curves will evaluate the specificity and sensitivity of the resulting echocardiographic, clinical, angiographic and laboratory biomarkers for the prediction of early and late mortality, and rehospitalization. A likelihood ratio test will be used to assess the additional increase in the chi-square value in order to evaluate the potential incremental prognostic value of novel imaging or laboratory parameters over baseline models. To assess the clinical prognosis of several groups of patients with specific echocardiographic or laboratory characteristics, a time-to-event analysis will be performed according to the Kaplan–Meier method. A log-rank test will be used to compare the event rates. The significance threshold for all statistical tests will be considered the two-tailed *p* value of 0.05. The outcomes will be reported with 95% confidence intervals. Data management and statistical analyses will be conducted using SPSS software, version 26 (IBM SPSS Statistics) and R version 3.4.4 (R Foundation for Statistical Computing, Vienna, Austria). 

To calculate the sample size of the study, the G*Power software version 3.1.9.6 was used. It was estimated that to detect an odds ratio > 1.5, approximately 500 patients with AMI will be required with a power of 90%, a statistical significance level < 0.05 and assuming a dropout rate of 20%. The sample size calculations were based on previously published studies on the evaluation of myocardial work indices in patients with AMI [19,20].

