## 2. Materials and Methods

### Study Design and Population

The ‘‘CLEAR-AMI’’ (ClinicalTrials.gov Identifier: NCT05791916) is a prospective, investigator-initiated, non-interventional study including patients with first AMI, ST-segment elevation myocardial infarction (STEMI) and Non-ST-segment elevation myocardial infarction (NSTEMI), hospitalized at the First Department of Cardiology of AHEPA University Hospital in Thessaloniki, Greece. All the patients undergo emergency coronary angiography in line with current guidelines [2]. The study adheres to the fundamental guidelines delineated in the Declaration of Helsinki [13] and the rules of good clinical practice, and has been approved by the Ethics Committee of the Aristotle University of Thessaloniki (reference number: 6.582/2022). The whole study design is presented in Figure 1.

This study aims to enroll a consecutive series of 500 patients presenting with first STEMI or NSTEMI and who are undergoing primary or emergency coronary angiography. A written informed consent is provided before enrollment for each eligible patient. Patients with a history of coronary artery disease, previous AMI or previous coronary intervention (percutaneous or surgical) will be excluded. Upon attaining the cohort of 500 patients, subgroup analyses will be conducted for NSTEMI and STEMI patients. The detailed eligibility criteria are described in Table 1.

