## 3. Data Collection and Study Procedures

Demographic characteristics, baseline medical history, medication, prior diagnostic and therapeutic interventions, and clinical presentation of hospitalization will be recorded for all patients. In addition, patient laboratory data including complete blood count, biochemical, hormonal and coagulation mechanism control, high sensitivity troponin T levels (hs-cTNT) (admission and peak values) and N-terminal pro-B-type natriuretic peptide values will be collected within 24 h upon admission and during hospitalization. Moreover, the traditional lipid profile of the participants will be collected in addition to Lipoprotein A, and apolipoproteins B and A1. Special emphasis is placed on the assessment of inflammatory markers, including high-sensitivity C-reactive protein (hs-CRP), neutrophil-to-lymphocyte ratio (NLR), interleukin-6 (IL-6), soluble urokinase plasminogen activator receptor (suPAR), and admission glucose value, in order to evaluate stress-induced hyperglycemia. The prognostic impact of the investigated inflammatory markers (hs-CRP, IL-6, SuPAR) will be adjusted for potential cofounding variables such as concomitant autoimmune diseases and acute nosocomial infections as appropriate.

Clinical characteristics and risk scores, including Killip Class, GRACE risk score, TIMI-STEMI and ΤΙΜΙ-NSTEMI will also be recorded. Additionally, the coronary angiography of eligible patients will be assessed by two independent experienced interventional cardiologists who will be blinded to the demographic and clinical patient features. Angiographic data such as lesion characteristics, SYNTAX score and coronary dominance will also be taken into consideration.

All the eligible patients with AMI will be invited to visit the hospital one month post-AMI for a stress ECG test using the treadmill test. The test will be performed while the patient is on medication to assess the drugs’ effectiveness, their exercise capacity, and the chronotropic competence.

The primary endpoint will be all-cause mortality. The secondary endpoints will include (i) cardiovascular mortality (ii) heart failure rehospitalization and (iii) a composite of cardiovascular mortality, non-fatal acute myocardial infarction, unplanned PCI and heart failure hospitalization.

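### Continuous baseline features are compared with an equal-variance test whose only stated exit is non-normality; Welch's test would be a safer default for groups of unequal size

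*Protocol article*

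**What the plan says.** Section 3.2 (Statistical Analysis) of the protocol article opens with the comparison of baseline clinical, echocardiographic, laboratory and angiographic features. Categorical features "will be examined and compared by the chi-square test for categorical variables for each group"; for the rest, "Student’s t-test, or the analysis of variance (ANOVA) will be used for continuous variables". There is one exit from these tests: "When assumptions of normality are not met, non-parametric tests (Mann–Whitney U, Wilcoxon etc.) will be performed". Unequal variances are not mentioned.

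The groups are not defined in that paragraph. The only subgroups named by clinical type are in Study Design and Population: "subgroup analyses will be conducted for NSTEMI and STEMI patients". Section 3.2 also refers, for the Kaplan–Meier analysis, to groups of patients with particular echocardiographic or laboratory characteristics.

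The search for predictors is described in the next paragraph and uses other methods: "Univariable and multivariable logistic regression analyses, and Cox regression analyses will be applied to identify independent predictors at follow-up". One threshold covers everything: "The significance threshold for all statistical tests will be considered the two-tailed *p* value of 0.05".

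**The concern.** Student's t-test and classical ANOVA estimate one common variance. When groups differ in size, the pooled estimate is dominated by the larger group. If the smaller group is in fact more variable, the standard error is too small and the p-value is too small. If it is less variable, the reverse holds and real mean differences are missed. Neither problem needs non-normal data, so the plan's only fallback would not be triggered.

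Unequal group sizes are plausible in this cohort. High-risk groups defined by a marker, or patients with and without an event, are unlikely to split evenly. The comparisons span four domains of features, each judged at 0.05, so a distorted p-value could recur across many of them.

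**Working it through.** **Inputs from the article:** enrolment of 500, an assumed dropout of 20%, and a two-sided threshold of 0.05. 500 × 0.80 = 400 evaluable patients.

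**Inputs assumed, because the article gives none:** the split between groups and the SD ratio (smaller group / larger group). Data are taken as normal with equal means. The larger group's SD is set to 1.

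**Formulas.** With n₁ in the smaller group, n₂ in the larger and SD ratio r:

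- True variance of the mean difference: r²/n₁ + 1/n₂.
- Variance used by the pooled test: [((n₁−1)r² + (n₂−1))/(n₁+n₂−2)] × (1/n₁ + 1/n₂).
- k = square root of (true / pooled). Actual two-sided error ≈ 2 × [1 − Φ(1.96/k)].

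**Smaller group more variable: 40 v 360, r = 1.5.**

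- True: 2.25/40 + 1/360 = 0.0590.
- Pooled: (39 × 2.25 + 359)/398 = 1.1225; × (1/40 + 1/360) = 0.0312.
- k = √(0.0590/0.0312) ≈ 1.376; 1.96/1.376 ≈ 1.424; error ≈ 15.4%. Simulation (20,000 replicates): 15.0%.

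**Smaller group less variable: 40 v 360, r = 0.67.**

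- True: 0.4489/40 + 1/360 = 0.0140.
- Pooled: (39 × 0.4489 + 359)/398 = 0.946; × 0.02778 = 0.0263.
- k ≈ 0.730; 1.96/0.730 ≈ 2.685; error ≈ 0.7%. Simulation: 0.8%.
- The cost here is power. With a difference set for about 80% power under Welch's test, simulation gave 79% for Welch and 54% for Student's t.

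**Range over splits.** The result depends on the share in the smaller group far more than on the total, so all 500 patients give much the same picture (simulated type I error, 40,000 trials per cell):

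| Split | r = 0.5 | r = 1.0 | r = 1.5 | r = 2.0 |
|---|---|---|---|---|
| 25 v 475 | 0.03% | 4.9% | 16.9% | 28.2% |
| 50 v 450 | 0.1% | 5.2% | 15.7% | 24.2% |
| 75 v 425 | 0.2% | 5.0% | 13.7% | 21.3% |
| 150 v 350 | 1.3% | 4.9% | 9.8% | 12.5% |
| 250 v 250 | 5.0% | 5.1% | 4.9% | 5.2% |

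Welch's test stayed between 4.8% and 5.3% in every cell. At 160 v 240, a near-balanced split such as STEMI v NSTEMI might give, Student's t ran from 3.6% to 8.3% over r = 0.67 to 2.0.

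The r = 1.0 column and the 250 v 250 row show the two conditions: sizes and SDs must both differ before the pooled test goes wrong.

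**The case against.** The strongest case against is that this is a textbook fact attached to a short sentence in a condensed article, about descriptive comparisons, with no evidence that variances differ. Much of that stands, and it rules out several stronger readings that a reader might infer.

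- **That the error enters covariate selection.** The rule is "Multivariate models will include only the co-variates that are significantly associated with the endpoint at univariate analysis". It directly follows the sentence on univariable and multivariable logistic and Cox regression, so the natural reading is that screening uses those models. The t-test belongs to the separate paragraph on baseline features.
- **That markers unrelated to outcome would appear prognostic.** A marker independent of death has the same distribution in those who die and those who survive, so its SD ratio is 1 and Student's t holds about 5% at any split. A marker with equal means but different SDs is related to outcome. The 15% is the error for the narrower hypothesis of equal means.
- **That deaths versus survivors is the planned comparison.** "The primary endpoint will be all-cause mortality", but the paragraph on group tests does not say that patients are split by it, and no death rate is given.
- **That reported 95% confidence intervals would be wrong.** Section 3.2 promises intervals for outcomes. Continuous variables are summarised by mean and SD or by median and quartiles, and no interval for a mean difference is planned.

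The appeal to condensation does not succeed. The article is not silent on the method: it names the test and names the one condition for leaving it. That is a stated choice and can be reviewed as such.

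**Conclusion.** The point holds in a narrow, conditional form and is minor. The plan fixes an equal-variance test for continuous baseline features with no provision for unequal variances. Where groups differ in both size and SD, p-values for mean differences can err in either direction with perfectly normal data: about 15% or about 1% against a nominal 5%, at an assumed 40 v 360 with SD ratios of 1.5 and 0.67. These splits and ratios are illustrations and do not come from the documents. It would be too strong to say that the p-values are wrong, since nothing in the documents shows that variances differ. The primary prognostic conclusions do not rest on these tests.

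**What to change.** In the first paragraph of section 3.2, replace Student's t-test and ANOVA with Welch's unequal-variance t-test and Welch's ANOVA. State that they are used by default, without a preliminary test of variances. The provision for non-normal data can stay as it is.

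The cost is one sentence. Welch's test is standard in both packages that the article names, the loss of power when variances are equal is negligible, and neither the data collected nor the sample size changes.

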Therefore, this study aims to identify clinical, laboratory, echocardiographic and angiographic features that could refine available risk assessment schemes post-AMI. The ultimate goal is to develop a contemporary predictive risk model that includes clinical parameters, angiographic characteristics, biochemical biomarkers of systemic inflammation and echocardiographic myocardial work indices to identify high-risk patients in the acute phase and predict downstream cardiovascular complications.

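### Admitting only univariably significant covariates to the multivariable models conflicts with the promised adjustment of inflammatory markers and will often drop the confounders named for it

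*Protocol article*

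**What the plan says.** All references are to the protocol article.

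- **Entry rule (3.2 Statistical Analysis):** "Multivariate models will include only the co-variates that are significantly associated with the endpoint at univariate analysis".
- **Threshold (3.2):** "The significance threshold for all statistical tests will be considered the two-tailed" p value of 0.05. No other screening threshold is given.
- **Use of the models (3.2):** "Cox regression analyses will be applied to identify independent predictors at follow-up", alongside univariable and multivariable logistic regression. A likelihood ratio test is to "evaluate the potential incremental prognostic value of novel imaging or laboratory parameters over baseline models".
- **Adjustment commitment (3. Data Collection and Study Procedures):** the prognostic impact of hs-CRP, IL-6 and suPAR "will be adjusted for potential cofounding variables such as concomitant autoimmune diseases and acute nosocomial infections as appropriate".
- **Aim (1. Introduction):** to "identify clinical, laboratory, echocardiographic and angiographic features that could refine available risk assessment schemes post-AMI".

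No section exempts the named confounders, or established predictors such as GRACE or LVEF, from the entry rule.

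**The concern.** The word 'only' makes a p value from this one sample the sole ground for entering a covariate. A confounder belongs in a model because of its relation to both marker and outcome, whether or not it reaches 0.05 alone. Autoimmune disease and hospital-acquired infection are probably uncommon in this cohort, and uncommon covariates are the ones that a significance screen misses. An analyst following the statistical section would then leave out what the data-collection section says will be adjusted for.

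Two further harms follow from the same rule. A predictor whose crude association is masked by another variable never reaches the model in which it would show. And a marker that enters because it was significant, and is then retested in the same patients, carries an over-optimistic estimate. At stake is what the study may claim when it calls a marker an independent predictor.

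**Working it through.** **Inputs from the article.** N about 500, dropout 20%, alpha 0.05 two-sided, power 90%, target OR 1.5. Evaluable patients: 500 × 0.80 = 400. **Assumed, because the article gives no figures:** event proportion 5-20%, confounder prevalence 3-10%, confounder OR 1.5 to 3.

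**1. The plan's own figure.** The article states that "to detect an odds ratio > 1.5, approximately 500 patients with AMI will be required with a power of 90" per cent. For a standardised continuous predictor in logistic regression, n = (z₁₋α/₂ + z₁₋β)² / [p(1−p)(ln OR)²]. With p = 0.20 this is (1.960 + 1.282)² / (0.16 × 0.1644) = 10.51 / 0.0263, about 400, and 400 / 0.80 = 500. The stated size is thus recovered at 20% events, a figure the article does not give; at 10% events the formula gives 711, or 889 with dropout. The present point needs only the 400.

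**2. Chance that a true confounder passes the screen, by hand.** Take prevalence 5% (20 exposed, 380 unexposed), OR 2, and 10% mortality in the unexposed.
- Exposed mortality: odds 2 × 0.1111 = 0.2222, so p = 0.182.
- SE(ln OR) = √[1/(20 × 0.182 × 0.818) + 1/(380 × 0.10 × 0.90)] = √(0.336 + 0.029) = 0.604.
- ln 2 / SE = 0.693 / 0.604 = 1.147. Pass probability = Φ(1.147 − 1.960) = 0.21.

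With 20% mortality in the unexposed, the SE is 0.491 and the pass probability is Φ(1.411 − 1.960) = 0.29.

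**3. Same quantity over the assumed ranges** (simulated chi-square screen, N = 400). The chi-square test is slightly more generous than the Wald test at such small exposed groups.

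| True OR of confounder | Retained by the screen |
|---|---|
| 1.5 | 11-21% |
| 2 | 18-48% |
| 3 | 32-86% |

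With two confounders (prevalence 5% and 10%, OR 2 each), both survive in 8% of studies at 10% events and 13% at 20% events.

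**4. Effect on a null marker.** The marker has no true effect but is raised by 1 SD by those two confounders (OR 2 or 3, events 10% or 20%). Type I error is 5.3-6.5% with screening and 4.8-5.5% with the confounders forced in. The median OR is 1.02-1.04 with screening and 1.00-1.01 when forced. The bias exists but is small.

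**5. Negative confounding.** Marker and confounder correlate at −0.6 and each has a true OR of 1.5 per SD. The marker's crude log OR is about 0.405 × (1 − 0.6) = 0.162.
- Passing the screen: √(400 × 0.09) × 0.162 = 0.97, so Φ(0.97 − 1.96) = 0.16 at 10% events. At 20% events, √(400 × 0.16) × 0.162 = 1.30, giving 0.25.
- Significant in the full model: the information is multiplied by 1 − 0.6² = 0.64. √(400 × 0.09 × 0.64) × 0.405 = 1.95, giving 0.49; at 20% events, 2.60, giving 0.74.

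Simulation agrees: the marker passes in 16-26% of studies, though it is significant in 48-73% of full models.

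**6. Selecting and retesting on the same data.** With 10 to 40 null candidates, correlated at 0 to 0.3, and 10% events, 49-94% of null markers that pass the screen remain significant in the multivariable model. That second step is therefore weak protection.

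**7. Likelihood ratio test for an unselected null marker.** With five correlated established predictors as baseline, type I error is 4.7-5.7% whether the baseline is screened or kept whole. Screening the baseline did not inflate it.

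**The case against.** The strongest reply is that the commitment to adjust ends with a proviso allowing discretion, that the rule drops a confounder only when it is non-significant, and that the harm in step 4 is slight. The first part fails: discretion about what is appropriate does not override 'only', and an analyst cannot tell which statement governs. The second stands: the rule can, and often will, drop a confounder, but it does not always do so. The third also stands for weak, uncommon confounders and a null marker, though not for step 5, which in turn rests on an assumed strong negative correlation.

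Three stronger readings are tempting and not supported.

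- **That the rule makes novel markers look incrementally useful.** Step 7 found no inflation for a marker that was not itself selected.
- **That chance builds the baseline models.** The article does not say that the screen defines them, and their content may be fixed in the analysis plan. A strong established predictor would usually pass anyway: at OR 2 per SD the pass probability is 86%, 99% and above 99% at 5%, 10% and 20% events. At OR 1.5 it is 42-90%.
- **That the rule is what fills the results with false predictors.** With 40 independent null markers, an assumed number, 1 − 0.95⁴⁰ = 87% of studies produce at least one false hit. Testing each marker against a fixed baseline gives about the same. That is multiplicity, a separate issue.

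**Conclusion.** The point holds in this form. The entry rule and the adjustment commitment cannot both be relied on. At OR 1.5 or 2, a true confounder was retained in fewer than half of studies in every scenario examined; at OR 3, retention ran from 32% to 86%. The rule can also lose a true predictor masked by negative confounding, and estimates for predictors selected and retested on the same data are over-optimistic.

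These sizes rest on 400 evaluable patients and on assumed event proportions, prevalences and odds ratios. They come from logistic calculations, taken as a guide to the Cox models as well. Inflated incremental value, or a large bias from dropping weak confounders, was not shown and is not claimed. The conflict of wording needs no assumption at all.

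**What to change.** 1. Delete the univariable-significance rule from 3.2.
2. Name an adjustment set in advance and force it in whatever its p values: an established risk score such as GRACE, plus LVEF, and for hs-CRP, IL-6 and suPAR also autoimmune disease and infection. This reconciles 3.2 with section 3.
3. Limit the number of terms by the expected events. At 400 evaluable patients, 5%, 10% and 20% mortality would give 20, 40 and 80 deaths.
4. Test each novel marker by likelihood ratio against that same fixed baseline model.
5. If any data-driven selection is kept, repeat the selection step inside internal validation.

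How the combined predictive model is built can stay as planned, since the article assigns that work to machine learning tools such as XGBoost.

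The cost is wording in the statistical section and a few degrees of freedom for the forced covariates. No new data are needed: the risk score and LVEF are already recorded, and the adjustment commitment already presupposes the confounder data. The study is described as ongoing, so the change should be made before the outcome analysis.
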